## Specific objectives

1. To assess the degree of disability, limitation of cervical mobility, perceived pain, cervical repositioning and electromyographic disturbances and degree of kinesiophobia and catastrophism in fighter pilots with flight-related neck pain.

2. To find out the possible associations according to age and flight experience with the clinimetric variables assessed.

3. To analyse the VFC in the take-off, flight and landing segments during emergency manoeuvres in the flight simulator.

4. To determine what changes occur during flight and which segment produces the greatest stress response in pilots.

5. Design and implement a multimodal physiotherapy programme combining supervised cervical exercise with laser-guided feedback (ELGF) and interferential current electro-massage (ICE).

6. To analyse the impact of the multimodal physiotherapy programme on variables analysed in the designed assessment protocol and on physiological changes using HRV.

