### Outcome Measures of Heart Rate Variability

Interbeat time interval (R-R) variation will be used to determine the autonomic modulation using Firstbeat Bodyguard equipment (Firstbeat Technologies, Jyväskylä, Finland). This device will be used to record HRV data for 20 min (at rest and during ICT application). Recordings will be exported from the devices to the computer via Firstbeat Uploader Software (Firstbeat Technologies) and analysed using Kubios Software (University of Eastern Finland, Kuopio, Finland). To calculate the autonomous balance, the HRV method based on the Poincaré plot will be used^32,33^. This software has proven to be extremely valid and capable of recording non-linear trends that are frequently present on R-R intervals of record^34^.

Time-domain variables:

- ***MeanHR (bpm):*** It corresponds to the interval between two beats (R peaks on the ECG).
- ***pNN50 (%):*** Percentage of consecutive RR intervals that differ by more than 50 ms from each other. A high value of pNN50 provides valuable information about high spontaneous heart rate (HR)^35^.
- ***Root Mean Square of the Successive Differences (rMSSD) (ms)***: The square root of the average of the sum of the differences squared between normal adjacent. It shows the degree of activation of the Parasympathetic Nervous System on the cardiovascular system. This parameter reports the short-term variations of the RR intervals. It is directly associated with short-term variability^35,36^.
- ***Min HR and Max HR (bpm)***: They indicate the minimum and maximum heart rate, respectively, using *N* beats.

Frequency-domain variables:

- ***Low-Frequency power (LF) (ms^2^):*** Situated between 0.04 and 0.15 Hz. In long-term recordings, it provides us with more information about the activity of the sympathetic nervous system (SNS)^35^.
- ***High-Frequency power (HF) (ms^2^):*** They are located between 0.15 and 0.4 Hz. HF is clearly related to the activity of the parasympathetic nervous system (PNS) activity and has a relaxation-related effect on HR^35^.
- ***Low/high-Frequency ratio (LF/HF):*** From the low-frequency and high-frequency ratios of the HRV spectral analysis results we can estimate the vagal (related to relaxation and HF) and sympathetic (related to stress and LF) influence. Thus, we can estimate sympathetic-vagal balance^35^.

Non-linear variables:

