- ***SD1 (ms):*** Sensitivity of short-term variability of the non-linear range of the HRV. It is considered an indicator of parasympathetic activity^32^.
- ***SD2 (ms)***: Long-term variability of the non-linear range of the HRV. It is a diameter from the Poincaré plot which indicates the degree of longitudinal dispersion. It is thought to reflect long-term changes in RR intervals and it is considered an inverse indicator of parasympathetic activity^32^.
- ***Stress Score (SS) (ms)***: It is an index described by Naranjo-Orellana et al.^32^ to facilitate the physiological interpretation of the Poincaré plot. It is expressed as the inverse of SD2 diameter multiplied by 1000.It is considered directly proportional to the sympathetic activity in the sinus node.
- ***Sympathetic/parasympathetic ratio (S/PS):*** It is also described by Naranjo-Orellana et al.^32^, S/PS is expressed as the quotient of SS and SD1. It is considered to reflect autonomic balance - that is, the relationship between sympathetic and parasympathetic activity.

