## Sample size

G*power 3.1 software will be used to calculate the sample size required to detect changes in the primary outcome (NPRS scale and JPSE). The calculations will be based on the detection differences of 2.5 points in the NPRS (MCID (minimal clinically important difference) (estimated for a variance in patients with neck pain of 10 points)^40^, assuming a standard deviation (SD) of 2.5 points.

Assuming an effect size (F-test) of 0.27 for ANOVA: repeated measures, within-between interaction groups differences, an alpha level of .05, and power of 80%, a total sample size of 30 participants will be estimated. The sample will be inflated by 10% to account for potential dropouts, resulting in a final target sample size of 34. This calculation showed that a sample size of 17 participants per group will be needed for a confidence interval of 95%, with a power of 80%, assuming a bilateral significance of .05.

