## Statistical Analysis

A descriptive analysis will be performed for each of the variables. The normality of the variables will be evaluated using the Shapiro-Wilk test, which showed a normal distribution for all the variables and, thus, parametric tests will be appropriate. Data will be reported as mean # SD. The demographic and clinical variables of the groups at baseline will be compared using the chi-square test for categorical data and the independent-samples t-test for quantitative data. A 2-way repeated measure analysis of variance will be performed to analyse the interaction effects of time (at baseline and post-treatment) in the 2 intervention groups (experimental and control group). The independent and paired-samples t tests will be used for comparisons between and within groups, respectively. Furthermore, the effect size will be calculated through Cohen's d coefficient. A value above 0.8 will be considered high; 0.5 moderate; and lower than 0.2 will be considered low^41^. Significance level will be established at p < 0.05. Data analysis will be made with the statistic software SPSS version 26.0 (SPSS Inc., Chicago, IL, USA).

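### HRV effect (specific objective 6, non-primary) is left to 12 variables with no lead and several unadjusted tests each; on the interaction alone the chance of a false positive is about 25% (13% to 43% over assumed correlations)

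*Protocol*

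**What the plan says.** The last item under Specific objectives is to analyse the programme's impact "on variables analysed in the designed assessment protocol and on physiological changes using HRV". HRV is therefore a stated efficacy question. It is not primary: the Sample size section powers the trial to "detect changes in the primary outcome (NPRS scale and JPSE").

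Outcome Measures of Heart Rate Variability lists 12 variables:

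- time domain (5): MeanHR, pNN50, rMSSD, Min HR, Max HR
- frequency domain (3): LF, HF, LF/HF
- non-linear (4): SD1, SD2, SS, S/PS

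None is named as leading. Recordings are planned in two conditions, at rest and during current application.

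The Statistical Analysis section fixes three kinds of test. "A 2-way repeated measure analysis of variance will be performed to analyse the interaction effects of time (at baseline and post-treatment") in the two groups. Then "The independent and paired-samples t tests will be used for comparisons between and within groups, respectively". One threshold covers everything: "Significance level will be established at p < 0.05". No order among the tests and no adjustment is given. The Sample size section makes the level two-sided ("assuming a bilateral significance of .05").

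**The concern.** Objective 6 has no decision rule beyond p < 0.05 on whichever HRV variable and test come out. With 12 variables and up to four tests each (interaction, post-treatment comparison, paired test in each arm), a nominal 5% level does not describe the risk of reporting an autonomic effect that is not there.

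A second issue concerns interpretation. Several listed variables carry the same information under different domain labels. rMSSD is a time-domain measure ("This parameter reports the short-term variations of the RR intervals") and SD1 a non-linear one ("Sensitivity of short-term variability of the non-linear range of the HRV"). If both move, it can look as though two methods agree when there is only one measurement.

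**Working it through.** **Inputs.** From the protocol: 12 HRV variables, the tests above, two-sided 0.05, and a target of 17 per arm. The Intervention section gives 14 and 17, which was also run. Not in the protocol, so assumed: correlation between HRV variables (0 to 0.9) and between visits (0.3 to 0.85). Each variable is counted once, although two recording conditions are planned.

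**The plan's own figure.** The protocol gives no HRV error rate. Its sample size does reproduce. With f = 0.27, two visits and an assumed correlation of 0.5, λ = f²·N·2/(1 − 0.5) = 0.0729 × 30 × 4 = 8.75, and power is 0.815 at N = 30 against 0.785 at N = 28. Then 30/0.9 = 33.3, rounded up to 34. So the trial is sized on the group-by-time interaction, which with two visits equals a t test on change.

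**Duplicates.**

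- By the protocol's definitions, SS = 1000/SD2 and S/PS = SS/SD1 = 1000/(SD1 × SD2). Both are fixed by SD1 and SD2.
- The protocol gives no formula for SD1. Mathematically, SD1 is the standard deviation of successive RR differences divided by √2. So SD1 = rMSSD/√2 when the mean successive difference is near zero. On a simulated RR series the ratio rMSSD/SD1 was 1.414, so the two give the same p-value.
- Distinct variables: 12 − 1 = 11 without SD1, and 9 if SS and S/PS are dropped too.

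**Independence benchmark, interaction only.** 1 − 0.95^k gives 37.0% for k = 9, 43.1% for k = 11 and 46.0% for k = 12. The last treats rMSSD and SD1 as separate tests, which they are not.

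**Simulation under no effect, 17 v 17, visit correlation 0.5.** Chance of at least one p < 0.05:

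| Variables | Correlation between them | Interaction only | + post-treatment t test | + paired, experimental | + paired, control |
|---|---|---|---|---|---|
| 11 | 0 | 42% | 65% | 76% | 83% |
| 11 | 0.5 | 31% | 50% | 60% | 69% |
| 11 | 0.7 | 23% | 38% | 48% | 56% |
| 11 | 0.9 | 14% | 25% | 32% | 38% |
| 9 | 0 | 38% | 59% | 70% | 78% |
| 9 | 0.5 | 28% | 45% | 56% | 64% |
| 9 | 0.9 | 14% | 23% | 30% | 36% |
| all 12, three shared factors, identities imposed | structured | 26% | 41% | 51% | 58% |

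The equal-correlation rows use 3,000 trials each and the structured row 10,000. A 10,000-trial repeat of selected equal-correlation settings agreed to within about 2 percentage points. Arms of 14 and 17 gave similar values. Over all settings the interaction alone runs from about 13% to 43%, and any of the four tests from about 36% to 85%.

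**One variable.** A single variable judged on all four tests already gives about 14% to 16%. Judged on the interaction only, it gives 5%.

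**The case against.** HRV is not primary, and a protocol commonly leaves multiplicity among non-primary outcomes to the SAP, which is not at hand. The protocol does not say that any one significant HRV variable will count as an autonomic effect. The same threshold also covers disability, catastrophizing, kinesiophobia and EMG. All of this is fair and keeps the point minor. It does not remove it: the protocol has its own analysis section, which fixes the tests and an unadjusted level for a stated objective without saying which result answers it.

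Three stronger readings are tempting and not supported.

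- A reader might infer that a false HRV effect would be reported more often than not, about 58% of the time. That value comes from one assumed correlation structure and counts the paired test in the control arm. That arm gets no intervention, so a change there is not evidence of a programme effect. Without that test the structured model gives about 49% to 53%.
- A reader might infer that the overlap of rMSSD and SD1 causes the inflation. It does the opposite: it removes a distinct test and lowers the rate. Its harm is apparent corroboration.
- A reader might infer that the authors intend to present SD1, SS and S/PS as independent confirmation. The protocol does not say so, and it openly defines SS and S/PS from other variables. Listing related indices side by side is not itself an error.

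Which HRV variable should lead is also the sponsor's choice, and Holm would control the error as well.

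**Conclusion.** The point holds in a limited form. The protocol gives objective 6 no lead HRV variable and several unranked tests per variable at an unadjusted 0.05. On the test that addresses a programme effect, the interaction, the false-positive chance across the family is about 25% in the structured model and 13% to 43% over assumed correlations of 0.9 to 0. It stays well above 5% under every assumption tried. Counting any of the four tests gives about 36% to 85%, but that total includes the control-arm paired test. These sizes rest on correlations that the protocol does not supply. The count of variables and tests, and the definitions of SS and S/PS, come from the protocol; the link between SD1 and rMSSD is mathematics. Severity is minor: the primary outcomes are untouched, and the correction is a cheap improvement.

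**What to change.** Before analysis, add a few sentences:

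- Name one HRV variable and one recording condition, of the sponsor's choice, as the outcome for objective 6. The condition must be recorded in both arms. Test it once, by the group-by-time interaction at two-sided 0.05, which gives a 5% false-positive rate. Alternatively, apply Holm across the distinct HRV interaction tests, which keeps the family rate at or below 5%.
- State that no HRV claim will rest on within-group tests.
- Report SD1 as a rescaling of rMSSD, and SS and S/PS as functions of SD1 and SD2, not as separate evidence.
- Label the remaining HRV variables exploratory, with 95% CIs for the between-group difference in change.

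No extra data or participants are needed. The cost is that the sponsor gives up significance claims on the other HRV variables or, under Holm, accepts a stricter threshold for each.
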